#### Presenteeism

The *Work Limitations Questionnaire* (WLQ) will assess performance and the degree to which health problems interfere with the ability to perform job roles [76]. Spanish [83] and Catalan [84] versions of the WLQ have been developed and validated. In the WLQ, respondents self-report levels of difficulty in performing 25 specific job roles across four scales, with scores expressed as an average of responses. The 5-item “Time Scale” addresses difficulty in scheduling demands. For the “Mental-Interpersonal Scale” six items cover difficulty performing cognitive tasks involving the processing of sensory information and interacting with others on the job. The “Output Scale” has five items exploring limitations in meeting demands for quantity, quality and timeliness of completed work. The nine-item “Physical Scale” assesses ability to perform job tasks that involve bodily strength, movement, endurance, coordination and flexibility.

Sub-scales scores are transformed to a 0–100 continuum to represent the amount of time in the previous 2 weeks affected by limited on-the-job performance (from a low to high rate of difficulty). These scales estimate work loss, known as the WLQ index [76], which is the weighted sum of the scores from the WLQ scales. In the present study, the WLQ index will be calculated by adding the scores of three WLQ scales; the “Physical Scale” will be excluded from the current analyses as it was not relevant to these job roles.

#### Job-related mental strain or work-related stress

The Job Content Questionnaire (JCQ) will measure work stressors [78]. This questionnaire follows the demand-control model and includes two dimensions: psychological demands of work and control over work. Work stress is expressed as the result of the interaction between both dimensions. The scale measures a third dimension – social support from co-workers, managers and supervisors – that can act as a moderator of the relationship between the demands of and control over one’s work [78].

The minimum reduced version of the questionnaire includes three dimensions: psychological demands (9 items), control over work (9 items) and support at work (11 items). The possible response categories for each of the items are: totally disagree (1), disagree (2), agree (3) and totally agree (4). The psychological demands dimension assesses workload, the intellectual demands and the time pressure. The control over work dimension assesses the possibility of making decisions, creativity and the application and development of one’s own skills. The support at work dimension assesses the support received from co-workers and supervisors.

The Spanish version of the minimum reduced version shows high reliability and content validity and moderate concept validity for each of the three dimensions [85]. Work stress is expressed as a ratio between psychological demands and control at work, with lower scores indicating less stress. The range of scores for the psychological demands dimensions varies between 12 and 48, while the score for the control at work dimension varies between 24 and 97 [74]. For the social support dimension, co-worker support will be measured by using a 5-item scale, while supervisor support will be measured with a 6-item scale on a 4-point Likert scale (1 = agree; 2 = somewhat agree; 3 = somewhat disagree; and 4 = disagree). Total social support is the sum of co-worker and supervisor support, with higher values reflecting greater perceived social support [78].

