	Waist circumferences (cm)	X	X	X	X	CV	Reduce
	*Systolic and Diastolic blood pressure*	X	X	X	X	CV	Reduce
**MENTAL WELL-BEING, WORK OUTCOMES**	Mental well-being (WEMWS)	X	X	X	X	CV	Increase
	Presenteeism (WLQ) and estimated work loss	X	X	X	X	CV	Reduce
	Sickness absence	X	X	X	X	CV	Reduce
	Work control, psychological demands, social support (JCQ)	X	X	X	X	CV	Increase
	Impact of work on employees´ health	X	X	X	X	CV	Improve

The anthropometric variables will be measured with an approved Seca 770 scale and a height measuring rod Seca 222. The BMI will be calculated by dividing the body weight by the square of the height in metres (kg/m^2^). Measurement of the waist circumference, in centimetres, will be completed using a stretch-resistant tape measure and recorded as the midpoint between the lower margin of the lowest palpable rib and the top of the iliac crest. The measurement will be repeated twice. If the measurements are within 1 cm of each other, the average will be calculated; and if the difference exceeds 1 cm, the two measurements will be repeated.

For systolic and diastolic blood pressure (BP), three measurements will be made, using the mean of the last two, with a validated OMRON M3 sphygmomanometer and following the recommendations of the European Society of Hypertension (https://www.eshonline.org/). The degree of metabolic control according to the percentage of HbA1c and basal glucose, lipid profile (total cholesterol total, HDL, LDL, triglycerides) will be measured by a preliminary blood test, and at the 6- and 12-month follow-ups.

At baseline, data from participants’ personal, social and work profile will be collected. Age, sex and social class will be recorded based on the clinical history and data from a questionnaire. A validated scale of occupation as an indicator of social class, according to the British Registrar General classification [86], will be used to record the highest level of completed studies, type of work, length of time working in the company, type of work contract, number of work hours and usual days of work.

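### The JCQ row of Table 1 counts rising psychological demands as a benefit, and the support items carry two opposite codings, so one-tailed tests of these two secondary scores could sit in the wrong tail

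*Protocol article*

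**What the plan says.** All places are in the Protocol article.

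- **Job-related mental strain or work-related stress, response coding.** The answer categories are given for all items as "totally disagree (1), disagree (2), agree (3) and totally agree (4"). Later in the same section co-worker support (5 items) and supervisor support (6 items) are described with a 4-point scale of "1 = agree; 2 = somewhat agree; 3 = somewhat disagree; and 4 = disagree". Total support is the sum of the two parts, "with higher values reflecting greater perceived social support". No reverse-scoring step is stated.
- **Same section, stress score.** Work stress is the ratio of demands to control, and a lower ratio means less stress.
- **Same section, ranges.** "The range of scores for the psychological demands dimensions varies between 12 and 48"; for control, "the score for the control at work dimension varies between 24 and 97".
- **Data collection methods, Table 1.** One continuous-variable row, "Work control, psychological demands, social support (JCQ"), measured at baseline and at 3, 6 and 12 months, has the single objective *Increase*. The demands/control ratio has no row.
- **Statistical methods.** The effect is measured on the continuous variables of Table 1. For some of them a higher mean counts as effective and for others a lower mean, and the article concludes from this that the test is one-tailed.

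**The concern.** A one-tailed test needs the correct favourable direction for every score before analysis. If the direction is wrong, the rejection region lies in the wrong tail: harm can be called benefit, and real benefit cannot be detected. A two-sided test with the wrong label can still be reinterpreted afterwards; a one-tailed test cannot.

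For the JCQ the text gives conflicting directions in two places. Demands are to rise according to Table 1, but a rise worsens the stress ratio as the scoring section defines it. Support has two opposite response codings and one stated interpretation, which for positively worded items fits only one of the codings. Work-related stress is a named secondary objective, so these scores will be reported as evidence about the programme.

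**Working it through.** **1. Demands.** Inputs: stress = demands / control, lower is better (scoring section); objective for demands = *Increase* (Table 1). Hold control at an illustrative 72 and raise demands from 24 to 36:

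- 24 / 72 = 0.333
- 36 / 72 = 0.500

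The change is a worsening by the scoring section and a success by Table 1. The two statements cannot both stand, and this needs no assumption about the instrument.

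**2. Support.** Inputs: 5 co-worker items and 6 supervisor items, each scored 1 to 4. Assumption: items are positively worded, so agreement means support. The sentence can be read as applying the reversed scale to all 11 items or only to the 6 supervisor items.

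| Coding | Full agreement | Full disagreement |
|---|---|---|
| General coding, all 11 items | 11 × 4 = 44 | 11 × 1 = 11 |
| Reversed scale, all 11 items | 11 × 1 = 11 | 11 × 4 = 44 |
| Reversed scale, 6 supervisor items only | 5 × 4 + 6 × 1 = 26 | 5 × 1 + 6 × 4 = 29 |

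On the second row a higher sum means less support, the opposite of the stated interpretation. On the third row the two halves largely cancel: the most and least supported respondents differ by 3 points, in the wrong direction. Whatever the item wording, the two codings run in opposite directions.

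**3. Consequence under a one-tailed test.** The article does not state alpha. A one-sided 0.05 reproduces its sample-size figures: at d = 0.5, 88 per arm (176 in total) gives one-sided power 0.951 (stated 0.95) and two-sided power 0.910 for the homogeneity test (stated 0.91), and 70 per arm gives one-sided power 0.903 (stated 0.90). I therefore assume one-sided 0.05.

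With n = 88 per arm, df = 174, critical value about 1.654 and noncentrality d × √(88/2) = d × √44:

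- Harm of d = 0.5 scored as benefit: noncentrality 0.5 × 6.633 = 3.317; probability of declaring benefit 0.95.
- Harm of d = 0.2 scored as benefit: noncentrality 0.2 × 6.633 = 1.327; probability 0.37.
- True benefit of d = 0.5 with the tail reversed: noncentrality −3.317; probability of detection about 4 × 10⁻⁷.

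These figures illustrate what a reversed tail does. They do not predict the JCQ effect in this trial.

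**4. Control range (minor).** For items scored 1 to 4, non-negative weights and no added constant, the maximum is four times the minimum, also when items are reversed as 5 − x. Demands: 4 × 12 = 48, as stated. Control: 4 × 24 = 96, not 97.

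**The case against.** **The ratio's direction is right.** The named outcome is work-related stress, and its definition as demands over control, lower being better, is explicit. This stands. A reader might infer that the work-stress tests as a whole point the wrong way; the documents do not support that. The exposure is limited to demands and support as separate scores, and would reach the ratio only if someone applied the row's *Increase* to it.

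**Direction is set by meaning, not by Table 1.** The Statistical methods section says the intervention works if the change is better in the intervention group, and the Objective column is partly shorthand (one entry is a dash, another is *Improve*). A careful analyst would notice that higher demands are not better. This lowers the chance of the error but does not remove the conflict. No other place gives directions variable by variable, and the column does distinguish them: presenteeism and sickness absence are marked *Reduce*.

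**Recoding may be left to the instrument's source.** The intended meaning of the support score is stated and agrees with Table 1, and a condensed article may omit a recoding step. That is fair as far as omission goes, and the documents do not show which coding is right. But the article states two opposite codings, which is a contradiction and not an omission.

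**The ranges do no harm.** A reader might infer from the figure of 97, or from nine items that would sum to 9–36, that the ratio has no fixed scale. That does not hold: the stated ranges already rule out a plain nine-item sum, a constant rescaling leaves a t-test unchanged, and 97 against 96 is a one-point slip that affects no test.

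**Conclusion.** Wrong as written on two counts: the Table 1 objective for demands contradicts the definition of work stress, and the support items have two opposite codings with no recoding stated. The first needs no outside assumption. That the second reverses or largely cancels the support score depends on positively worded items and no unreported recoding.

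Taken literally with the one-tailed rule, a rise in demands or a fall in support could be declared a benefit, with probability 0.95 at d = 0.5 and 0.37 at d = 0.2 (88 per arm, assumed one-sided alpha of 0.05). If each score is tested at 3, 6 and 12 months, at most 2 × 3 = 6 tests are exposed. All are secondary; the primary outcomes and the sample size are untouched. It should be corrected before analysis because the error is easy to make and cheap to prevent.

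**What to change.** 1. Split the JCQ row of Table 1 into four: control (increase), psychological demands (decrease), social support (increase) and demands/control ratio (decrease).
2. Reconcile the two support codings against the instrument actually used. State one coding, say whether it covers co-worker items, supervisor items or both, and name any reverse-scored items, so that a higher sum does mean more support.
3. Alternatively, or in addition, test these scores two-sided. This removes the wrong-tail risk, and at d = 0.5 with 88 per arm it lowers power from 0.95 to 0.91. It does not settle what a higher support sum means, so step 2 is still needed.
4. As a minor correction, check the upper limit of the control range, which by the arithmetic above should be 96 if the minimum is 24.

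The cost is wording in the scoring section and Table 1. No new data are needed.

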#### Employees’ work-related health problems

Six questions from the 6th European Working Conditions Survey will measure work-related health problems [77]. Patients will be asked if they have suffered, in the last 3 months, any of the following health problems: backache, muscle pain in the shoulders, neck and/or upper limbs muscle pain in the lower limbs anxiety, general tiredness or general health problems [77]. The results will be given in percentages.

#### Employees´ sickness absence

Two questions will be asked [77] in relation to the number of work days the patient has missed, in the last 3 months, due to sick leave or health reasons, and how many of these days were caused by work-related health problems (excluding accidents) [77]. The results will be reported as a percentage of patients that have missed a day of work and the average number of days of temporary disability.

### Participant timeline

The intervention group will have access to the automated W@W-App for 13 weeks. The control group will be asked to continue their routine daily activities receiving usual health care. All participants will receive the usual health recommendations and general information on the health benefits of sitting less and moving more through an infographic (Additional file 1). Figure 10 shows the planned follow-up visits to be carried out by the healthcare professionals, the variables to be measured and the tasks to be performed in each follow-up visit.

**Fig. 10 Fig10:**
[figure not shown]
Participants’ timeline for the Walk@Work-App study protocol of a randomized controlled trial

### Data collection methods

The data collection will be carried out at the beginning and at 3, 6 and 12 months using the activPAL3TM device, data from the computerized medical history and a survey. At 6 and 12 months, each patient will have a blood test done for the clinical variables (Table 1). In each measurement, the participants will be summoned in consultation to record the subjective and objective habitual and occupational sedentary behaviour and the subjective and objective habitual and occupational level of physical activity.

**Table 1 Tab1:** Data collection methods for the Walk@Work-App study protocol of a randomized controlled trial

	Variables	Baseline	Follow-up			Variable type	Objective
		**t = 0** **Months**	**t = 3 Months**	**t = 6 Months**	**t = 12 Months**		
**PARTICIPANT CHARACTERTISTICS**	Socio-labour level	X				QV	Factors that can affect the final result
	Number of working hours	X				CV	
	Changes in glucose-lowering dose within last 3 months		X	X	X	QV	
	Antidiabetic drugs or insulin	X	X	X	X	QV	
	Type of insulin	X	X	X	X	QV	
	Diet	X	X	X	X	QV	
	Change in diet		X	X	X	QV	
**HABITUAL AND OCUPATIONAL SEDENTARY BEHAVIOUR AND PHYSICAL ACTIVITY**	Total sitting time, workday, weekend (ActivPAL3TM)	X	X	X	X	CV	Reduce
	Number of sitting time interruptions workdays, weekend (ActivPAL3TM)	X	X	X	X	CV	Increase
	Sedentary bouts < 20 minutes workdays, weekend (ActivPAL3TM)	X	X	X	X	CV	Reduce long periods of sitting/ increase short periods of sitting
	Sedentary bouts 20–40 minutes workdays, weekend (ActivPAL3TM)	X	X	X	X	CV	
	Sedentary bouts 40–60 minutes workdays, weekend (ActivPAL3TM)	X	X	X	X	CV	
	Sedentary bouts > 60 minutes workdays, weekend (ActivPAL3TM)	X	X	X	X	CV	
	Standing time workdays, weekend (ActivPAL3TM)	X	X	X	X	CV	Reduce
	Activity time workdays, weekend (ActivPAL3TM)	X	X	X	X	CV	Increase
	Light-intensity physical activity workday, weekend (ActivPAL3TM)	X	X	X	X	CV	Increase
	Moderate-to-vigorous physical activity workday, weekend (ActivPAL3TM)	X	X	X	X	CV	Increase
	Sufficiently or insufficiently active (SBPAAT)	X	X	X	X	CV	Increase
	Domain-specific sedentary behaviour (WSQ)	X	X	X	X	CV	Reduce
	Glycaemic index (mg/dl)	X		X	X	CV	Reduce
	HbA1C (%)	X		X	X	CV	Reduce
**LIPID PROFILE**	Total Cholesterol (mg/dl)	X		X	X	CV	Reduce
	HDL (mg/dl)	X		X	X	CV	Increase
	LDL (mg/dl)	X		X	X	CV	Reduce
	Triglycerides (mg/dl)	X		X	X	CV	Reduce
**ANTHROPOMETRIICS**	Weight (Kg)	X	X	X	X	CV	Reduce
	Height (cm)	X	X	X	X	CV	–
	BMI (kg/m^2^)	X	X	X	X	CV	Reduce
	Waist circumferences (cm)	X	X	X	X	CV	Reduce
	*Systolic and Diastolic blood pressure*	X	X	X	X	CV	Reduce
**MENTAL WELL-BEING, WORK OUTCOMES**	Mental well-being (WEMWS)	X	X	X	X	CV	Increase
	Presenteeism (WLQ) and estimated work loss	X	X	X	X	CV	Reduce
	Sickness absence	X	X	X	X	CV	Reduce
	Work control, psychological demands, social support (JCQ)	X	X	X	X	CV	Increase
	Impact of work on employees´ health	X	X	X	X	CV	Improve

The anthropometric variables will be measured with an approved Seca 770 scale and a height measuring rod Seca 222. The BMI will be calculated by dividing the body weight by the square of the height in metres (kg/m^2^). Measurement of the waist circumference, in centimetres, will be completed using a stretch-resistant tape measure and recorded as the midpoint between the lower margin of the lowest palpable rib and the top of the iliac crest. The measurement will be repeated twice. If the measurements are within 1 cm of each other, the average will be calculated; and if the difference exceeds 1 cm, the two measurements will be repeated.

For systolic and diastolic blood pressure (BP), three measurements will be made, using the mean of the last two, with a validated OMRON M3 sphygmomanometer and following the recommendations of the European Society of Hypertension (https://www.eshonline.org/). The degree of metabolic control according to the percentage of HbA1c and basal glucose, lipid profile (total cholesterol total, HDL, LDL, triglycerides) will be measured by a preliminary blood test, and at the 6- and 12-month follow-ups.

At baseline, data from participants’ personal, social and work profile will be collected. Age, sex and social class will be recorded based on the clinical history and data from a questionnaire. A validated scale of occupation as an indicator of social class, according to the British Registrar General classification [86], will be used to record the highest level of completed studies, type of work, length of time working in the company, type of work contract, number of work hours and usual days of work.

Changes in glucose-lowering therapy within the last 3 months, the type of oral antidiabetic drug or insulin, type of insulin, if participants follow a special diet or have modified their diet in the last 3 months will be also recorded. These variables will describe participants and, when the data is processed and if some outlier is observed, to justify possible unusual behaviours. Table 1 shows the variables and its type recorded at each instant: continuous or qualitative variables.

SBPAAT: Brief Physical Activity Assessment Tool; WSQ: Workforce Sitting Questionnaire; BMI: Body mass index; HbA1c: glycosylated haemoglobin A1c; HDL: High-density lipoprotein; LDL: Low-density lipoprotein; WEMWS: Warwick-Edinburgh Mental Well-being Scale; WLQ: Work Limitations Questionnaire; JCQ: Job-related mental strain; Continuous variable (CV), Qualitative variable (QV).

### Statistical methods

A descriptive study of all the measured variables will contain the mean, standard deviation, minimum and maximum value and dispersion coefficient. The homogeneity of the intervention and control group at the initial moment – that is, that there are no statistically significant differences between the two groups in any of the variables measured – will be verified by performing a two-tailed test of means for independent samples for each variable (Additional file 2).

The effect of the mHealth W@W-App programme will be measured by continuous variables (Table 1) which will be used to evaluate the differences between before and after implementing the mHealth programme. In some variables, the programme will be effective if the mean increases in the intervention group while for other variables effectiveness will happen if the mean decreases. For example, the programme will be effective if physical activity increases and total cholesterol decreases. Therefore a one-tailed test of means will be performed. For these continuous variables, the difference of the variable between moment t of the measurement and the initial moment will be calculated, (*X*_*Dt*_ = *X*_*t*_ − *X*_0_), which quantifies whether there have been changes, after t months, associated with the intervention. The intervention has a positive effect if the results of the intervention group are significantly better than those of the control group; that is, if the values of the variable *X*_*Dt*_ are better in the intervention group. The qualitative variables (see Table 1) will be used to check if any patients display unusual behaviour that are due to changes in their medication or diet [86]. Intention-to treat analysis will be used. The statistical tests to be carried out in the event that homogeneity between the groups is not accepted while the procedure is outlined in Additional file 3.

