### Objectives

In this context, the main objective of this protocol for a randomized controlled trial is to assess the effectiveness in the short-medium and long term of a mHealth programme to “sit less and move more” at work on reducing sedentary behaviour and increasing habitual and work physical activity in office staff with DM2. The secondary objectives are to evaluate the effectiveness of the programme on i) clinical variables: glycaemic control and lipid profile; ii) anthropometric and blood pressure variables; iii) improvement in mental well-being, presenteeism, absenteeism and work-related stress.

This is important given the scarcity of studies that evaluate the effectiveness of mHealth programmes in reducing sedentary behaviour as a therapeutic approach for people with chronic pathology, specifically with DM2, which also evaluate the global health impact of the mHealth intervention on clinical parameters, mental well-being and productivity [46]. This study will make it possible to clarify whether people diagnosed with one of the most prevalent chronic diseases, DM2, are likely to benefit from the implementation of mHealth interventions by healthcare professionals in a wide range of health variables and through the use of objective measures of habitual and occupational sedentary behaviour [49].

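### Effect tests are one-tailed, and the only table of directions lists psychological demands as an increase, against the protocol's own scoring of work stress

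*Protocol article*

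**What the plan says.** Statistical methods uses a two-tailed test only for baseline homogeneity. The programme effect is assessed on the continuous variables of Table 1, as the change from baseline compared between arms. On direction it says: "In some variables, the programme will be effective if the mean increases in the intervention group while for other variables effectiveness will happen if the" (the sentence closes by naming a fall in the average). It then concludes: "Therefore a one-tailed test of means will be performed". The intervention is judged to have a positive effect if its changes are significantly better than those of the control group.

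Table 1 (Data collection methods) has an Objective column with entries such as *Reduce* and *Increase*. One row reads: "Work control, psychological demands, social support (JCQ) X X X X CV Increase". The standing-time row carries *Reduce*.

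The section on job-related mental strain states: "Work stress is expressed as a ratio between psychological demands and control at work, with lower scores indicating less stress". Objectives lists among the secondary aims "improvement in mental well-being, presenteeism, absenteeism and work-related stress".

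**The concern.** A one-tailed test is only as good as its pre-set direction. Psychological demands are the numerator of the stress ratio. With control unchanged, higher demands therefore mean more stress, the opposite of the stated aim. An analyst who took the tail from Table 1 would count rising demands as benefit and could not detect falling demands.

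The wider issue does not depend on the JCQ row. The reason given for one tail is that benefit is a rise for some outcomes and a fall for others. That defines benefit for each outcome, but it does not show that a change the other way is impossible or of no interest. Under the plan, a worsening of HbA1c, blood pressure, well-being or weekend sitting has no formal test.

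Standing time adds a smaller doubt. *Reduce* is given without a reason, while some of the programme's strategies get people out of the chair. If standing rose, a test in the *Reduce* direction could not show it.

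**Working it through.** **Passages side by side**

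- Table 1: psychological demands share one row, and one *Increase*, with work control and social support.
- Job-related mental strain section: stress = demands / control, lower is better. A rise in demands raises the ratio and a rise in control lowers it, so one direction cannot be favourable for both.
- Objectives: work-related stress is to improve, so the ratio should fall.

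*Increase* therefore fits control and contradicts the scoring for demands.

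**Inputs from Sample size:** 176 evaluable patients (88 per arm), medium effect d = 0.5, power 0.95; 220 recruited for 20% loss; power 0.90 if only 140 remain; power 0.91 for the homogeneity test at 176. Alpha is not stated, and 0.05 is assumed.

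**Method:** two-sample t-test with n per arm, df = 2n − 2, noncentrality δ = d·√(n/2).

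- One-sided power = P(T > t(0.95, df)), with T noncentral t with parameter δ.
- Two-sided power = P(|T| > t(0.975, df)).

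**Reproducing the protocol's figures**

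- n = 88: df = 174, δ = 0.5·√44 = 3.317. The critical value is 1.654 one-sided, giving power 0.951 (stated 0.95), and 1.974 two-sided, giving 0.910 (stated 0.91 for the two-tailed homogeneity test).
- n = 70: df = 138, δ = 0.5·√35 = 2.958. One-sided power is 0.903 (stated 0.90); two-sided it is 0.836.
- Recruitment: 176 / 0.8 = 220, as stated.

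The effect-test figures thus match one-sided 0.05. Two-sided 0.10 would give the same 0.951 at 88 per arm, so the match supports the assumed alpha without proving it.

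**If demands are tested as *Increase*** (88 per arm, one-sided 0.05; for 0.2 SD, δ = 0.2·√44 = 1.327)

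| True effect on demands | P(significant, planned tail) | P(significant, two-sided 0.05) |
|---|---|---|
| Rise of 0.5 SD (worse) | 0.951 | 0.910 |
| Rise of 0.2 SD (worse) | 0.373 | 0.261 |
| Fall of 0.2 SD (better) | 0.0015 | 0.261 |
| Fall of 0.5 SD (better) | about 4 × 10⁻⁷ | 0.910 |

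In the two-sided column, the sign of the estimate shows whether a significant result is harm or benefit. The same figures apply in mirror image to standing time tested as *Reduce*: a true 0.5 SD rise would have practically no chance of being shown.

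**Power after the change to two-sided 0.05, d = 0.5**

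- 88 per arm: 0.951 becomes 0.910.
- 70 per arm: 0.903 becomes 0.836.
- All 220 evaluable (110 per arm): 0.980 becomes 0.958.
- Keeping 0.95 would need 105 per arm, 210 evaluable; 210 / 0.8 = 262.5, so 263 recruited.

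**The case against.** The strongest reply is that Statistical methods never ties the tail to the Objective column. It refers to Table 1 for which variables are continuous or qualitative, and its decision rule is that results be better in the intervention group. Since the JCQ section defines lower stress as better, an analyst could set the sign correctly. The column is also not a complete list of tails: height has a dash and impact of work has only *Improve*. This stands, and it means a reader may not infer that the trial is bound to call rising demands a success. It does not remove the contradiction. No other list of directions exists, and correcting the sign at analysis would depart from the printed table, possibly after the data are seen.

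It is also fair that the entry looks like shorthand for a merged row, that it concerns a secondary objective, and that the directions for total sitting and for activity agree with the aims.

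A reader might infer that *Reduce* for standing is wrong. The documents do not show that: the programme's quantified goals replace sitting with moving or stepping, and standing could fall at the same time. A reader might also question *Increase* for sitting interruptions, but that matches the stated focus on breaking up prolonged sitting.

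Finally, a pre-declared one-sided test is a disclosed choice, and worsening would remain visible in the planned descriptive statistics. That is true, but visibility is not a test.

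**Conclusion.** The point holds in this form. The protocol fixes one-tailed effect tests, and its only table of directions contradicts its own scoring for psychological demands. If the table is followed, a 0.5 SD worsening is declared a success with probability 0.95, and a 0.5 SD improvement has almost no chance of significance, against 0.91 two-sided. For the other outcomes, the loss is that worsening cannot be formally shown. The standing-time direction is unexplained rather than wrong.

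The figures assume 88 evaluable patients per arm, equal variances, one-sided alpha 0.05 (inferred from the stated sizes and powers), and that the Objective column is used to choose the tail. The contradiction between table and text, and the general limit of one-tailed tests, need none of these assumptions.

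**What to change.** 1. In Statistical methods, make all between-group effect tests two-sided at 0.05, state that alpha, and report 95% confidence intervals.
2. In Table 1, split the JCQ row: demands and the demand/control ratio *Reduce*; control and social support *Increase*. While doing so, check the scoring of support. The JCQ section codes those items from 1 = agree to 4 = disagree, yet says higher totals mean more support.
3. Give a reason for *Reduce* on standing time, or drop the direction.
4. In Sample size, restate power at d = 0.5 as 0.91 with 176 evaluable and 0.84 with 140.

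The cost is wording and a less favourable stated power (0.95 to 0.91, and 0.90 to 0.84), with no added patients. Only if 0.95 must be kept does recruitment rise, from 220 to 263. It should not be assumed that adjusting for baseline would win the power back: that depends on the correlation between baseline and follow-up, which the protocol does not give.
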